### Sample size calculation and recruitment

We aim to examine 76 participants (phase 1: 20, phase 2: 56). The sample size for phase 1 follows recommendations for feasibility pilot studies, as the purpose of phase 1 is to test procedures for phase 2 [48,49].

Sample size calculations for phase 2 were based on a repeated measures design and calculated with G*Power. Based on similar study setups [27], we anticipate a medium effect size of approximately *d* = .40 [50] resulting in a total sample size of *N* = 51 (parameters: *d* = .40, alpha = .05, 1 – beta = .80). To compensate for dropouts and possible technical issues leading to missing data (especially motion capture data) we will recruit 10% additional participants, resulting in a total sample of *N* = 56.

Recruitment for both phases is carried out and monitored by the study team. Phase 1 is currently being conducted (from June 2025 until the anticipated completion at the end of November 2025), phase 2 is planned to begin in January 2026 and continue for eight months. Each participant will be offered a compensation of €20. Alternatively, participating students can receive course credits.

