
At the end of the lab session in phase 1, participants are interviewed about the experimental procedure to obtain qualitative feedback on the quality of the simulated back pain and the overall acceptance of the back pain simulator and the motion capture suit (see Additional File 2). The experiment will be conducted by two trained experimenters. Standardization will be ensured throughout the procedure. To maintain protocol adherence, experimenters follow a detailed checklist during the lab session, which also includes comment sections for any deviations from the protocol. If participants abort during the study, they will be asked about the reason, and their data will be excluded from analyses.

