### Statistical methods

Qualitative analysis on feasibility and acceptability in phase 1 will be carried out with MAXQDA Analytics Pro [80]. Data of phase 2 will be analyzed using a repeated-measures design. Correlations of dependent variables will determine if multivariate analyses of variance (MANOVAs) or separate analyses of variance (ANOVAs) are indicated, following common recommendations of moderate intercorrelation [81].

The first MANOVA will include the within-subjects factor *condition* (PainSim + vs. PainSim-) and dependent variables measuring task-related fear of movement, pain intensity, impairment and emotional distress. A second MANOVA will assess *mobility* (LROM, LF, MV). And a third MANOVA will examine stress (HRV, salivary cortisol, salivary amylase, subjective stress) in the same manner. Psychophysiological data (e.g., HRV-data) that deviate (significantly) from the other data (i.e., outliers) will be excluded in accordance with the established practices in the literature. The pattern of missing data is tested with MCAR-test. If the missing data is missing completely at random, we will conduct multiple imputation.

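### Multiple imputation is made conditional on data being missing completely at random, which is the wrong gate, and no method is named when that condition fails

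*Protocol article*

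**What the plan says.** The Statistical methods section of the protocol article sets out a two-step rule. First, "The pattern of missing data is tested with MCAR-test". Then, "If the missing data is missing completely at random, we will conduct multiple imputation". The test level is not given, and the section says nothing about what follows if the data are judged not to be MCAR.

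Two other places bear on the rule. Under Sample size calculation and recruitment, the authors expect dropouts and technical losses, chiefly in motion capture, and add an allowance: "we will recruit 10% additional participants, resulting in a total sample of *N* = 56". Under Lab appointment, participants who stop early are removed: "If participants abort during the study, they will be asked about the reason, and their data will be excluded from analyses". Neither place alters the imputation rule.

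**The concern.** Multiple imputation is valid under MAR, given the variables in the imputation model. That is a weaker requirement than MCAR. Making MCAR the entry condition calls for imputation where it is least needed for bias, and does not call for it once the test signals that missingness is selective.

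The planned analyses are within-subject MANOVAs or ANOVAs. Without imputation, their standard form uses only participants with complete values in both conditions. If missing PainSim+ values are related to how a person moved or responded in PainSim-, the remaining pairs are a selected group and the estimated condition difference can shift.

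The test is also a poor judge. At N = 56 a non-significant result may simply reflect low power, so the gate is unreliable in both directions.

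**Working it through.** **The plan's own figures.** Inputs from the sample size section: "parameters: *d* = .40, alpha = .05, 1 – beta = .80". A two-sided paired t-test with d = 0.40 has power 0.7999 at N = 51 (0.80 as rounded; 52 gives 0.808). The allowance is 51 × 1.10 = 56.1, stated as 56. These figures reproduce, and nothing below changes them.

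**Assumptions, because the article gives no missing-data inputs.** N = 56 pairs; both conditions have SD 1; PainSim- is fully observed with mean 0; PainSim+ has mean −0.40. The correlation ρ between conditions is 0.3, 0.5 or 0.7. (A difference of 0.40 SD equals the planned d = 0.40 only at ρ = 0.5, where the SD of the difference is √(2 − 2ρ) = 1.) PainSim+ is missing with log-odds c ± 1.0 × (PainSim- value). With c = ln(0.12/0.88), 12% are missing at the mean and 15.6% overall. A lower c gives 12% overall.

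**Complete cases, by formula.** Given the PainSim- value y, the expected difference is −0.40 + (ρ − 1)y. Averaging over those still observed:

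complete-case mean = −0.40 − (1 − ρ) × m,

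where m is the mean PainSim- value among the observed. Numerical integration gives m = ∓0.108 at 12% missing and ∓0.138 at 15.6%. The sign is negative when higher values go missing and positive when lower ones do.

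| ρ | Missing | Higher values missing | Lower values missing |
|---|---|---|---|
| 0.3 | 12% | −0.325 | −0.475 |
| 0.3 | 15.6% | −0.304 | −0.496 |
| 0.5 | 12% | −0.346 | −0.454 |
| 0.5 | 15.6% | −0.331 | −0.469 |
| 0.7 | 12% | −0.368 | −0.432 |
| 0.7 | 15.6% | −0.359 | −0.441 |

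Example: ρ = 0.5, 15.6%, higher values missing: −0.40 − 0.5 × (−0.138) = −0.331. The bias runs from 0.032 to 0.096 SD, which is 8% to 24% of 0.40, in either direction.

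**Simulation of the same settings** (5,000 runs each). Complete cases agree with the table to within 0.005. Regression imputation of PainSim+ from the observed PainSim- value gives about −0.40 throughout.

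**How often the selectivity is noticed.** A t-test comparing PainSim- between those with and without a PainSim+ value rejects in about 58–69% of runs at log-odds 1.0 and in about 22% at log-odds 0.5. This checks one known driver. It is not the multivariate MCAR test that the article names.

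**A second set-up with a Little-type MCAR test** (3,000 runs per setting; 20 imputations; ρ = 0.5). Missingness depends on an observed auxiliary variable correlated −0.6 with PainSim+ and −0.2 with PainSim-, at log-odds 1 or 2 per SD.

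- MCAR, 10–30% missing: bias at most 0.003 for both methods. The SD of the estimate is 0.145–0.153 for complete cases and 0.141–0.144 for imputation, so the gain is precision only.
- MAR, 10% missing: complete-case bias 0.038 to 0.056; imputation at most 0.002; the test rejects in 42–84% of runs, so it misses the mechanism in 16–58%.
- MAR, 20–30% missing: complete-case bias 0.069 to 0.148; imputation at most 0.001; the test rejects in 65–100%.

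**The case against.** Imputing under MCAR is valid and recovers some precision, so the stated branch does no harm in itself. The anticipated losses are largely technical and may be close to MCAR, where the rule does impute. The study is a single lab visit, and those who abort, probably the most selective loss, are excluded under a separate rule. All of this stands and limits the likely practical effect. It does not make MCAR the right condition for imputation.

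Four stronger readings are tempting, and the document does not support them.

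- A reader might infer that imputation is forbidden outside MCAR and that the plan commits to complete cases. The text is silent on that branch; complete cases are the natural default, not a stated choice.
- A reader might say that complete cases are biased whenever MCAR fails. They can be; it depends on the mechanism. Standard imputation in turn does not repair missingness that depends on the unobserved value (MNAR).
- A reader might claim that the effect would be exaggerated by a set amount, for instance −0.47 in place of −0.40. That needs ρ = 0.5, about 16% missing and lower values going missing. Reversing the direction gives −0.33, so the sign is not established.
- A reader might charge the rule with heavy listwise losses: with four outcomes in two conditions, 1 − 0.98⁸ = 15% at 2% missing per value, or 1 − 0.95⁸ = 34% at 5%. Those sums assume independent missingness, which is the case where the plan imputes. They also fit mobility poorly: its three measures come from the same recordings, so a 5% failure rate per condition loses 1 − 0.95² = 9.8%, about what the 10% allowance covers.

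**Conclusion.** The rule is wrong as written, rather than merely short on detail. It ties multiple imputation to the one mechanism under which complete cases are already unbiased, and leaves open what happens when the test points to selective missingness. Nothing else in the article corrects it.

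The size is illustrative. Under the assumed inputs above, a complete-case default would be off by roughly 0.03 to 0.10 SD on a true difference of 0.40 SD, in a direction that cannot be known beforehand, while imputation from the observed data removes the bias if MAR holds. These figures rest on assumed missing rates, correlations and strength of dependence. That MCAR is the wrong gate rests on none of them.

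**What to change.** Remove the MCAR test as a gate (it may still be reported descriptively) and replace the rule with text such as: missing values will be handled under MAR by multiple imputation, or by a likelihood-based mixed model using all available observations, whatever the MCAR test shows. The model will include condition, order, the outcomes of the given analysis in both conditions, and a small set of baseline predictors of missingness. Complete-case results and a simple MNAR check will be reported as sensitivity analyses.

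Keep the predictor set small, since N = 56 will not support a large imputation model. State also how this fits with the exclusion of participants who abort under Lab appointment; otherwise that exclusion stands beside the new rule unreconciled.

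The cost is a few sentences and modest analysis time. It needs no new data and no change to the sample size, and should be settled before phase 2 outcomes are analysed.

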## Discussion

With the planned study, we aim to establish an experimental paradigm to investigate the association of pain, FA, actual movement patterns, and acute stress responses in healthy samples under controlled pain conditions. We will realize this by employing a back pain simulator for the first time. The results of our study will provide insights in the acceptability and feasibility of simulating lower back pain.

Since the implementation of a back pain simulator is novel, the limitation of the study consists in the lack of validation of the back pain simulator. Nonetheless, we will provide initial insights into the use of this methodological approach. First tests with ten pain-free people indicated behavioral changes similar to pain patients. Further, this approach will allow us to make future studies as comfortable as possible for pain patients, thus improving prospective adherence.

Our study has two notable implications: First, it is the first study to mechanically induce lower back pain to examine mobility impairments. Second and most importantly, it integrates the assessment of pain, actual movement patterns, FA, and related stress responses measured with novel motion capture technologies.

Results of the study will set the cornerstone for future studies to not only induce pain, but also FA itself (e.g., through instructions). Our further research will focus on establishing a paradigm to reliably distinct high and low fear avoidant movement patterns with novel motion capture technologies. In the long term, such paradigms may contribute to a deeper understanding of the interplay of psychological and physiological mechanisms not only in induced pain but also in genuine CPLBP.

## Abbreviations

ADS-L: General Depression Scale (Allgemeine Depressionsskala)
AEQ: Avoidance-Endurance Questionnaire
ANS: Autonomic nervous system
BMI: Body mass index
BPS: Back Performance Scale
CLBP: Chronic low back pain
CPLBP: Chronic primary low back pain
ECG: Electrocardiogram
EmpkinS: Empatho-Kinaesthetic Sensor Technology
ER: Endurance-responses
FA: Fear avoidance
FAR: Fear-avoidance responses
FESV: Emotional pain processing questionnaire (Fragebogen zur Emotionalen Schmerz-verarbeitung)
GERT: GERonTologic simulator
HPA: Hypothalamic-pituitary-adrenal
HR: Heart rate
HRV: Heart rate variability
ICD: International Classification of Diseases
IMU: Inertial measurement unit
LBP: Low back pain
LF: Lumbar flexion
LROM: Lumbar range of motion
MV: Movement velocity
PainSim: Pain simulator
PCS: Pain Catastrophizing Scale
PSS-10: Perceived Stress Scale (10 item version)
sEMGt: Surface electromyography
SSSQ(-G): Short Stress State questionnaire (German Version)
STST: Sit-to-stand task
TSK(-G): Tampa Scale for Kinesiophobia (for the general population)
VAS: Visual analogue scale
WSQ: Web Screening Questionnaire for Common Mental Disorders
